### **13.1.3.5 Microarray Analysis**

mRNA will be extracted from vaginal epithelial cells and gene expression changes determined using a human GeneChip array (Affymetrix, Santa Clara, CA). Probe level data will be generated using Affymetrix Command Console v1.1. Probes will be summarized to gene level data in Partek Genomics Suite v6.5 (Partek, St. Louis, MO) using the Robust Multi-array Analysis (RMA) algorithm (Irizarry, 2003). A list of genes will be filtered to only include genes differentially expressed by at least 2-fold between treatment phases within an individual. Analysis of functional networks will be carried out with Ingenuity Pathway Analysis 8.5 Software (Ingenuity Systems, Redwood city, CA, USA).

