## **6 STUDY DESIGN**

The study population will consist of post-menopausal subjects presenting with intermediate Nugent Scores (4-6). The study duration is 47 days with a final follow-up at 129 days. A total of fourteen (14) subjects will be randomized into this exploratory study.

Subjects will undergo the following treatment phases:

- Two weeks of no treatment (Days 1-15); followed by
- Three days in which each subject randomly receives either two intravaginal placebo capsules or two intravaginal probiotic capsules (Days 16-18) each day; followed by
- 18 day wash-out period; followed by
- Three days in which each subject randomly receives either two intravaginal placebo capsules or two intravaginal probiotic capsules (Days 37-39) each day; and
- Follow-up approximately 90 days after last treatment.

The capsules given on Days 37-39 will not be the same as the capsules given on Days 16-18. During one treatment period the probiotic will be given and during the other treatment period, placebo will be given. Not the subject nor the study staff will know which capsules contain the probiotics.

INHP (placebo or probiotic) consists of capsules to be administered vaginally on study treatment days; once in the morning and once in the evening approximately 12 hours apart.

Following the first two weeks of no treatment, subjects will be given six (6) placebo or probiotic capsules, on Day 15, to be administered vaginally twice daily for 3 consecutive days. Panty liners will be given to use on treatment days. On Day 36, subjects will again be given six (6) placebo or probiotic treatment capsules to be administered vaginally twice daily for

3 consecutive days in the same manner. A diary to track compliance and to rate general vaginal discomfort and record any other adverse events will be given to the patients and reviewed by the study Investigator or designee at the following visit. Subjects that remain colonized with the probiotic strains at Day 47 will return for a follow-up visit on Day 129. During the follow-up phase, all subjects who received treatment will be queried monthly via telephone regarding adverse events on a monthly basis until Day 129. See Section 8 for visit details.

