### **Secondary Objectives:**

Determine the effect of *L. rhamnosus* GR-1® and *L. reuteri* RC-14® on the subjects' anti-microbial defences and vaginal comfort as measured by:

- Microbial ecology analysis, human genetic microarrays and multiplex immunological assessments; and
- An increase in symptom relief such as itching, irritation, or general vaginal discomfort.

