## **6.2 Exploratory Outcomes**

- Metagenomic study to evaluate whether there is an increased abundance of lactobacilli and decrease in pathogens with probiotic therapy;
- Metabolomic study to determine whether there are differences in the factors associated with improved health between probiotic, placebo, and no treatment conditions;
- Multiplex immunological study to evaluate the modulation of an anti-microbial and/or anti-inflammatory in the host in response to the probiotic;
- Microarray analysis to determine whether there are differences in gene regulation between probiotic, placebo, and no treatment conditions; and
- Symptom analysis to evaluate whether probiotic treatment is associated with symptom relief.

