### ***Visit 2- Day 5 (+ 1 day)***

The following assessments will be performed:

- Subject diaries will be reviewed and subjects queried regarding any adverse events the subject may have experienced;
- A vaginal health questionnaire will be completed;
- Five (5) vaginal samples in the following order:
  - one swab for Nugent Score/microbiota analysis;
  - one swab for multiplex immunologic analysis;
  - one cytobrush sample for metabolomic analysis;
  - one cytobrush sample to evaluate host gene regulation;
  - one swab for microbiota analysis;
- A vaginal pH measurement will be taken in the same manner as described for Visit 1;
- Review concomitant medications; and
- An appointment will be scheduled for Day 15 visit.

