#### **Treatment Phase II - Visit 6 – Day 36 (+/-2 days)**

The following assessments will be performed:

- Subjects will be queried regarding any adverse events they may have experienced;
- A vaginal health questionnaire will be completed;
- Five (5) vaginal samples and a vaginal pH measurement will be taken in the same manner as described for Visit 2;

- Subjects that have a Nugent Score of 4 – 6 will then be given either six (6) placebo or six (6) probiotic capsules per the randomization and will be instructed to administer them vaginally two (2) times daily for the next 3 consecutive days. Written instructions for product administration will be provided. Panty liners will be supplied to use on treatment days;
- Subjects will be instructed to keep the capsules in the container and refrigerated until use;
- Subjects will be given a diary to track compliance and to rate any general vaginal discomfort and record any other adverse events;
- Review concomitant medications; and
- An appointment will be scheduled to return in 4 days (5 days is acceptable) for Day 40 visit.

*Subjects with a Nugent Score of 7 – 10 at Visit 6 will be treated for BV as appropriate by the Investigator and discontinued from the study. End of treatment assessments and procedures (Visit 8) should be done.*

*Subjects with a Nugent Score of 0 – 3 at Visit 6 will be discontinued from treatment. If these subjects are still colonized with at least one of the probiotic strains they will return for a final study visit on Day 129. All subjects discontinued from treatment will be queried via telephone regarding adverse events on a monthly basis until Day 129.*

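### The stated microarray gene list rests on a 2-fold change within one woman, a rule that cannot separate product from time and carries no error control

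*Protocol*

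**What the plan says.** Section 6.2 gives the aim: "Microarray analysis to determine whether there are differences in gene regulation between probiotic, placebo, and no treatment conditions". Section 6.1 also names human genetic microarrays under a secondary objective.

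Section 13.1.3.5 describes the array platform, summarization to gene level by RMA, and then a single selection step: "A list of genes will be filtered to only include genes differentially expressed by at least 2-fold between treatment phases within an individual". The next and last step is the pathway work: "Analysis of functional networks will be carried out with Ingenuity Pathway Analysis 8.5 Software". The section mentions no test, no variance estimate, no false discovery rate and no rule for combining the women's lists. Sections 13.1.3.1 to 13.1.3.3 (Nugent score, pH, symptoms) call for a comparison of the test articles; the microarray section speaks of treatment phases.

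Three design features bear on the rule:
- Section 6 puts the untreated phase first for every woman: "Two weeks of no treatment (Days 1-15); followed by".
- The crossover is described as "During one treatment period the probiotic will be given and during the other treatment period, placebo will be given".
- The visit schedule takes "one cytobrush sample to evaluate host gene regulation" at each of Visits 1 to 8. Visits 1-3 precede any dose, Visits 4-5 follow the first course, Visit 6 is the pre-dose visit of Phase II, and Visits 7-8 follow the second course.

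**The concern.** A fold-change cut-off applied woman by woman discards what the randomized crossover offers. Only women from both sequences, taken together, allow the product effect to be separated from the period effect, and the rule never takes them together. A fold-change cut-off also ignores how variable each gene is, so among unchanged genes the noisiest pass most often.

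At stake is the reading of the gene list and of the networks built on it. A network could reflect drift over seven weeks, or sampling and array noise, and still be reported as a response to the probiotic.

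**Working it through.** The protocol states no error rate or power for this analysis, so there is no figure to reproduce. Two properties of the stated rule can be checked.

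**1. Product against time (no outside figures needed).** For one gene on the log2 scale, let δ be the probiotic-minus-placebo effect and π the change from Phase I to Phase II.
- Probiotic first: Phase II − Phase I = π − δ.
- Placebo first: Phase II − Phase I = π + δ.

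A single woman supplies one equation for two unknowns. With δ = 0 and π = 1, every woman has an expected 2-fold change with no product effect. Across the two sequences, half the difference of the means gives δ and half their sum gives π. For either product against no treatment, the untreated phase is earlier in every woman, so not even the two sequences remove the time change.

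**2. Unchanged genes that pass.** Assumptions that are not in the protocol: 20,000 unchanged genes, independent normal errors, per-array within-woman log2 SD s. With m arrays averaged per phase,

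P(pass) = 2 × [1 − Φ(1 / (s√(2/m)))].

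Worked case, s = 0.3 and m = 1: s√2 = 0.424; 1/0.424 = 2.36; P = 0.0184; 0.0184 × 20,000 ≈ 368.

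| s | P, 1 array | genes, 1 array | P, 2 arrays | genes, 2 arrays |
|---|---|---|---|---|
| 0.2 | 0.0004 | 8 | <0.0001 | about 0 |
| 0.3 | 0.0184 | 368 | 0.0009 | 17 |
| 0.5 | 0.1573 | 3,146 | 0.0455 | 910 |

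These counts are for one phase pair in one woman.

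**3. Both together.** For a time shift t with no product effect and one array per phase, P(pass) = 1 − Φ((1 − t)/(s√2)) + Φ((−1 − t)/(s√2)). For t = 0.5 this is 12% at s = 0.3 and 26% at s = 0.5. For t = 1 it is 50% at both.

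**4. Does a group-level contrast work here?** A simulation compared Phase II minus Phase I differences between sequences by a t-test. It assumed 7 women per sequence, all complete, one array per phase and a time shift of 0.5 log2. Per-gene type I error was 0.049 to 0.051. For a true 2-fold product effect:

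| s | power at p<0.05 | power at p<0.001 |
|---|---|---|
| 0.3 | >0.99 | >0.99 |
| 0.5 | >0.99 | 0.79 |
| 0.7 | 0.93 | 0.37 |

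An unadjusted 5% test would still pass 0.05 × 20,000 = 1,000 unchanged genes, so multiplicity control is needed as well.

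**The case against.** The strongest answer is that a full statistical analysis plan is announced in section 13.1 and is not at hand. Testing, error control and the combining of women are commonly placed there, and section 13.1.3.5 does not say that its filter is the only step. That stands as far as it goes: nobody can say from the protocol that no test will be run. But the protocol does fix a selection rule and its direct use in pathway analysis. If the analysis plan adds a test, this section has to be reconciled with it.

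Four stronger readings are tempting, and the protocol does not support them.
- *There is no replication.* Host-gene samples are taken at eight visits, so each phase has repeat samples, and 14 women are planned. It is the filter that makes no stated use of them.
- *There is no probiotic-placebo contrast.* Section 6.2 names one, and Phase I against Phase II within a woman is nominally that contrast. The defect is that it is inseparable from period at that level.
- *The list will be mostly noise.* The count depends on an SD, a gene number and an array number that the protocol does not give. It is small at an SD of 0.2, and averaging two arrays cuts it sharply.
- *Noise accumulates over all 14 women.* That presumes that a gene passing in any one woman enters a common list, which the section does not say.

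The study is also a pilot with no formal sample size. That excuses low power, but not a rule that cannot attribute a change to the product.

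**Conclusion.** The point holds in this form: as written, the per-woman 2-fold rule does not answer the question in section 6.2, because product is confounded with period inside each woman and no treatment is confounded with time in all of them. This follows from the design alone.

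The absence of a variance estimate and of error control in the stated rule is a second defect, whose size is uncertain. It ranges from negligible (about 0 to 8 unchanged genes per comparison at an SD of 0.2) to severe (910 to 3,146 at an SD of 0.5), depending on the assumed SD and on whether arrays are averaged.

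The consequence is limited to an exploratory analysis that is also named under a secondary objective. The change should be made, but the primary Nugent analysis does not depend on it.

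**What to change.** Rewrite the selection step in section 13.1.3.5 as follows.
- For each gene, fit a moderated mixed model to the log2 values of all women, with condition (no treatment, probiotic, placebo) and period as fixed effects and woman as a random effect. Because no treatment occupies only the first period, code period as Phase II against Phase I.
- Name the samples: Visits 4-5 and 7-8 as post-dose, Visits 1-3 as no treatment.
- Make probiotic against placebo the main contrast. Report contrasts with no treatment, and describe them as confounded with time.
- Control the false discovery rate at a prespecified level, for example 10%.
- Keep the 2-fold rule as an additional effect-size filter, and send only genes that pass both to pathway analysis.
- Keep women who have no Phase II treatment in the model. Section 8.1 states that subjects with a "Nugent Score of 0 – 3 at Visit 6 will be discontinued from treatment", so an analysis of complete pairs alone would drop women because of their Nugent result.

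The cost is analysis wording only; samples and arrays stay the same. The downside is a shorter, possibly empty, gene list. Power will be below the simulated values where women have no probiotic-placebo pair, since the simulation took all 14 as complete and used a simple t-test rather than this model. As in any two-period crossover, the contrast also assumes no carry-over.

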### **13.1.3.6 Metabolomic Analysis**

The metabolomic samples will be analyzed by GC-MS, LC-MS and NMR to determine small molecule profiles in the vaginal cavity. Molecules such as short chain fatty acids, metabolic intermediates, hormones and other signaling molecules can be detected using these techniques. The small molecule profile will be compared between treatments within a subject and can be used to provide information on the biological changes associated with probiotic treatment.

### **13.1.3.7 Multiplex Immunological Analysis**

Levels of immunological cytokines will be measured using a multiplex antibody based approach. Detection of specific cytokines will be analyzed using flow cytometry based techniques. The cytokines will be quantitated and levels compared between treatments.

### **13.1.4 Safety Analysis**

Safety analysis will be completed utilizing the data in the Safety Set as defined in Section 13.1.1. Adverse events occurring during the study and follow-up will be tabulated by Body System, severity, and Investigator reported relationship to the INHP. Any deaths or serious INHP associated AE cases will be summarized.

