**Visit 9 – Day 129 (+/-7 days) Additional Follow-Up**

Subjects who are still colonized with at least one of the probiotic strains at Visit 8 (or at Visit 6 if they discontinued treatment at that time) will return for a final study visit. The following assessments will be performed:

- Subject will be queried regarding any adverse events they may have experienced; and
- One (1) vaginal swab will be taken in the same manner as the microbiota swab described in Section 8.2. This swab will not be used to perform the microbiota analysis however; the swab will only be used to determine whether the subject continues to be colonized by the probiotic.

Follow-up will be conducted for all treated subjects (including those that were discontinued). All treated subjects will be queried via telephone regarding adverse events on a monthly basis until Day 129.

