## **13 STATISTICS**

### **13.1 Statistical Methods**

A complete statistical analysis plan will be finalized prior to the enrolment of the first subject into the study. All analyses and summaries, in table and graph form, will be presented by treatment group, unless specified otherwise.

Frequency distributions (n, proportions) will be used to present categorical data such as Nugent Scores and symptoms. Descriptive statistics such as n, mean, minimum, maximum, median and standard deviation (SD) will be used to present continuous variables such as age. No statistical sample size testing was performed.

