#### **13.1.1 Analysis Populations**

**Safety Set:** All randomized subjects who received the INHP at any dose or placebo, will be included in the safety analyses.

**Full Analysis Set:** All randomized subjects will be analyzed following the principle of intention-to-treat (ITT) provided they received the INHP or placebo and had at least one efficacy observation after first insertion.

**Per protocol Set:** All subjects who are compliant with the study protocol (i.e., who do not experience any major protocol deviations), who received the INHP or placebo and had at least one efficacy observation after first insertion.

The primary efficacy analysis will be based on the Full Analysis Set, although a secondary analysis will also be performed based upon the Per-Protocol Set (if there are differences) to assess the sensitivity of the analysis to the choice of analysis population.

The analyses of all other efficacy endpoints will be based upon the Full Analysis Set only. All safety analyses will be based upon the Safety Set.

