## **13.2 Sample Size and Power Considerations**

No formal sample size calculation was performed for this study. The number of subjects to be randomized is based on feasibility and practical considerations for such an exploratory study. It is planned that a total of fourteen (14) subjects will be randomized in this study.

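### Pooling adverse events to Day 129 by treatment group does not assure comparable product frequencies in a crossover with 21 days after the first product and 93 after the second

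*Protocol*

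**What the plan says.** Five statements in the protocol combine here.

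- Section 13.1.4 sets the time span of the safety table: "Adverse events occurring during the study and follow-up will be tabulated by Body System, severity, and Investigator reported relationship to the INHP".
- Section 13.1 sets how it is laid out: "All analyses and summaries, in table and graph form, will be presented by treatment group, unless specified otherwise". Section 13.1.4 does not specify anything else.
- Section 13.1.1 defines a single Safety Set: "All randomized subjects who received the INHP at any dose or placebo, will be included in the safety analyses".
- Section 8.1 (Visit 6) stops treatment for women with a Nugent Score of 0-3, and adds: "All subjects discontinued from treatment will be queried via telephone regarding adverse events on a monthly basis until Day 129". Women with 7-10 at that visit are also discontinued before the second product.
- Section 8.1 (Visit 9) extends collection to everyone treated, explicitly including discontinued women: "All treated subjects will be queried via telephone regarding adverse events on a monthly basis until Day 129".

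The synopsis makes the type, frequency and severity of adverse events the safety measure. Section 6 places dosing on Days 16-18 and Days 37-39, with opposite products. No section gives a per-product window, a rule that assigns an event to a product, or a product-specific denominator.

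**The concern.** A single pooled window shown by treatment group suits a parallel-group trial, where each woman has one product and the same follow-up. Here each woman is meant to have both products, with a short observation period after the first and a long one after the second. Some women have only one product and all the remaining time.

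Who has only one product depends on the Nugent Score at Visit 6, which is the measure the probiotic is meant to change. The number of days behind each product column can therefore depend on efficacy. With 14 women, a few events that reflect days observed and not the product would change how the table reads. Events late in follow-up also come after both products in most women, so any single-product label on them is arbitrary.

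**Working it through.** **Calendar (section 6; section 8.1).** The protocol's own figures reproduce: washout Days 19-36 is 36 - 19 + 1 = 18 days, and follow-up after the last capsule is 129 - 39 = 90 days. Counting from first capsule:

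- first product: 36 - 16 + 1 = 21 days;
- second product: 129 - 37 + 1 = 93 days, or 93/21 = 4.4 times as long;
- woman stopped at Visit 6: 129 - 16 + 1 = 114 days after her only product.

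**Assumptions.** Each event is charged to the most recent product (not stated in the protocol). Daily risk is equal on both products. Stopping rates are not given and are varied. On numbers, section 13.2 says "It is planned that a total of fourteen (14) subjects will be randomized in this study"; section 7.2 gives no sequence ratio, so 7:7 is assumed first and then varied.

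**Formula.** Let nA and nP be the women starting on probiotic and placebo, and fA and fP the shares stopped at Visit 6 for any reason.

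- Probiotic days = nA[114fA + 21(1 - fA)] + 93nP(1 - fP)
- Placebo days = nP[114fP + 21(1 - fP)] + 93nA(1 - fA)

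At 7:7 these reduce to 798 + 651(fA - fP) and 798 - 651(fA - fP), because 7 × 114 = 798 and 7 × 93 = 651. Only the difference in stopping matters.

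**Results at 7:7.**

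| Stopping, probiotic-first v placebo-first | Probiotic days | Placebo days | Ratio |
|---|---|---|---|
| none, or equal | 798 | 798 | 1.00 |
| 50% v 20% | 993.3 | 602.7 | 1.65 |
| 3/7 v 1/7 | 984 | 612 | 1.61 |
| 4/7 v 1/7 | 1077 | 519 | 2.08 |
| 1/7 v 3/7 | 612 | 984 | 0.62 |

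**Stops for 7-10.** Take the 50% v 20% row as stops for 0-3 only and add stops for 7-10:

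- 20% after placebo, none after probiotic: totals 50% v 40%, 798 ± 65.1 = 863.1 v 732.9, ratio 1.18;
- 20% after placebo, 10% after probiotic: totals 60% v 40%, 798 ± 130.2 = 928.2 v 667.8, ratio 1.39;
- 40% after placebo, 10% after probiotic: totals 60% v 60%, ratio 1.00.

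**Unbalanced sequences, no stopping.** At 9:5, probiotic has 9 × 21 + 5 × 93 = 654 days and placebo 5 × 21 + 9 × 93 = 942, ratio 0.69. At 5:9 the ratio is 942/654 = 1.44.

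**Denominator.** In the 50% v 20% case, 7 + 7(0.8) = 12.6 women on average receive probiotic and 7 + 7(0.5) = 10.5 placebo. Dividing both columns by 14 leaves the ratio at 1.65. Dividing by women exposed gives 993.3/12.6 = 78.8 v 602.7/10.5 = 57.4 days per woman, ratio 1.37. An exposed-women denominator alone does not remove the imbalance.

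**Women with at least one event.** With an assumed risk of 10% per 30 days, the chance is 7.1% in 21 days, 27.9% in 93 and 33.0% in 114. With 4/7 v 1/7 stopping, the expected numbers are 3.20 v 1.59 women, or 24.7% of 13 exposed v 15.9% of 10, with no true difference.

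**Attribution.** In a woman who takes both products, Days 40-129 follow both. Section 5.3.2.2 reports non-detection of the strains only at 30 days after oral use; the washout here is 18 days after vaginal use.

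**The case against.** The strongest reply is that section 13.1.4 is silent on attribution, that presentation by treatment comes only from a general default, and that such detail usually sits in the SAP, which section 13.1 promises before first enrolment. Part of this stands: charging events to the last product is an assumption of this check. But the protocol does fix the pooled span, the single set and the by-treatment layout, and that combination suits a crossover badly.

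Several stronger readings are tempting and are not supported.

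- A reader might infer that the products inherently have unequal observation time. The inequality belongs to the period; balanced sequences with equal stopping give equal totals.
- A reader might infer that the probiotic column must show an excess. The visit rule also stops women at 7-10. If the probiotic works, those stops should be commoner after placebo, which offsets the effect. Section 5.1.3 describes intermediate women as about equally likely to move to either side.
- A reader might infer that percentages are taken on all 14 women. Section 13.1.1 says who enters the safety analyses, not what each product column is divided by. Nor would a denominator of 14 offset the excess: it leaves the ratio unchanged.
- A reader might infer that events on Days 1-15 are charged to a product. They are queried at Visits 2 and 3, but nothing places them in a product column, and section 11.3 excludes serious events before product.

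Finally, no between-product safety test is planned, and this is a small pilot; section 13.2 says "No formal sample size calculation was performed for this study". That limits the consequence. It does not make a frequency table with uneven windows easier to read.

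**Conclusion.** The concern holds conditionally. The pooled table gives comparable product frequencies when sequences and Visit 6 stopping are balanced (or imbalances happen to offset), and the protocol secures neither. Section 7.2 states no ratio, and stopping depends on a score the probiotic is meant to lower. If the effect lasts to Visit 6, stopping for 0-3 will differ by first product.

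Under the assumed rates, the ratio of observed days is about 1.65 for 50% v 20% total stopping, 1.18 to 1.39 with the smaller 7-10 offsets shown, and 0.69 or 1.44 for a 9:5 or 5:9 split without stopping. All these figures rest on last-product attribution and on assumed rates. The 21, 93 and 114 days come from the protocol's calendar. The attribution problem after Day 39 needs no such assumption: it applies to every woman who takes both products, even with equal totals.

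**What to change.** In section 13.1.4, and in the SAP table shells, tabulate events by product in the same window for both periods: first capsule to the one-week visit, Visit 5 or Visit 8. Nominally this is Days 16-26 and Days 37-47, 11 days each. Use the women who received that product as the denominator. Show the no-treatment phase, the remaining washout and the telephone follow-up to Day 129 separately, by sequence.

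This uses data already collected and needs no new visits. The cost is one more table split and fewer events in each product column. It does not remove possible carry-over into the second-period window.
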